#### Care during the antenatal period, labour and the postnatal stay of both groups

In order to meet the above requirements for care of women participating in the study, each hospital should be able to perform continuous fetal heart rate monitoring in labour, be able to perform fetal scalp pH for an abnormal fetal heart rate trace, have on-site skilled obstetric, anaesthetic and paediatric staff, able to perform emergency caesarean section, have available a consultant obstetrician for emergency back-up, and be able to cross match blood [48,49]. Care for the woman and baby will be by the primary caregivers.

#### Follow up after birth until the time of primary hospital discharge for both groups

After birth information will be obtained relating to birth and infant outcomes from the woman and infant's case notes. The birth form will be completed after the woman has given birth. Similarly the postnatal and neonatal forms will be completed for live born infants after discharge of both mother and baby from hospital.

Longer-term follow up for both groups:

Longer-term follow up of all women is currently planned to assess maternal physical and emotional health, wellbeing and child development.

### Primary Study Endpoints

Serious adverse outcomes for the infant defined as:

Perinatal/Neonatal Mortality (defined as any fetal death after study entry or death of a liveborn infant within 28 days of age (excluding lethal congenital anomalies); or Serious neonatal morbidity (defined as one or more of the following, excluding lethal congenital anomalies: birth trauma (subdural or intracerebral haemorrhage, spinal cord injury, basal skull fracture, other fracture, peripheral nerve injury present at discharge from hospital); seizures at <24 hours age or requiring two or more drugs to control; Apgar score <4 at 5 minutes; cord pH<7.18; base deficit <-8 (arterial or venous cord blood); neonatal encephalopathy stage 3 (Sarnat & Sarnat 1976); admission to the neonatal intensive care unit (NICU) > 4 days; severe neonatal lung disease (defined as MAP >10 and or FiO_2 _>0.80 with need for ventilation); proven necrotising enterocolitis; proven systemic infection in first 48 hours of life treated with antibiotics).

Definitions of adverse outcome are those used by the Australian and New Zealand Neonatal Network [60] and those considered by experts as important measures of term and post-term neonatal morbidity [61].

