### Sample Size

The incidence of serious adverse infant outcome is the primary endpoint of the study. The true risk of serious adverse infant outcome is estimated as 1.6% for planned elective, repeat caesarean birth [62]. It is proposed that sufficient women are recruited to provide reliable evidence about the effects of a policy of planned VBAC compared with a policy of planned elective, repeat caesarean on serious adverse infant outcomes. The sample size will detect a change in risk from 1.6% to 3.6% as suggested by the systematic reviews [31]. If the ratio of ERC to VBAC is 1:1 a study of 2180 women would have an 80% power of detecting a statistically significant difference at an alpha level of 0.05 (two tailed). Our pilot study has suggested a ratio of 5.5:4.5. Allowing for an ERC to VBAC ratio of 6.5:3.5 and a small loss to follow up (1%) the sample size required will be 2314 women.

The expected rate of serious maternal complications for planned elective repeat caesarean section is likely to be higher than the 3.9% found in the planned caesarean section arm of the Term Breech Trial [62]. Systematic reviews of the cohort studies of VBAC compared with elective repeat caesarean section provide an estimate of the risks for serious maternal complications of 7.7% [31]. A sample size of 2314 women will have 80% power (2-tailed alpha error of 0.05) of finding the following increases in risk for serious maternal complications: 16% to 20.6%, 12% to 16.1%, 8% to 11.5%, 6% to 9.1% and 4% to 6.7%.

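### The base-deficit item of the primary endpoint pairs a term and a sign that disagree, so read literally it selects alkalosis instead of acidosis

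*Protocol article*

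**What the plan says.** The protocol article, under Primary Study Endpoints, defines the primary outcome as perinatal or neonatal death, or serious morbidity. The morbidity part is "Serious neonatal morbidity (defined as one or more of the following, excluding lethal congenital anomalies"), so a single item is enough. The two acid-base items are adjacent and separated by a semicolon: "cord pH<7.18; base deficit <-8 (arterial or venous cord blood"). The second of them, "base deficit <-8 (arterial or venous cord blood"), is given without a unit.

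The section refers to outside sources for its definitions ("Definitions of adverse outcome are those used by the Australian and New Zealand Neonatal Network [60"], together with a set of expert-derived measures), but does not reproduce them. The article nowhere uses the term base excess, defines base deficit as a negative quantity, or states the criterion a second time.

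**The concern.** Base deficit and base excess are one measurement with opposite signs. A limit of the form below -8 belongs to base excess. Attached to base deficit, it points to the opposite disturbance from the one that the neighbouring pH item is looking for.

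This is a stated rule in the primary endpoint, and it can make an infant an event on its own. Outcomes are taken from case notes onto study forms (Follow up after birth) in a multicentre study. If the rule is programmed as written, an infant whose value is entered as base excess -10 counts, while the same infant entered as base deficit +10 does not. The classification would then depend on a recording convention that the article does not fix.

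**Working it through.** **1. The plan's own figures, to see whether the item enters them.** Inputs from Sample Size: p1 = 0.016 ("The true risk of serious adverse infant outcome is estimated as 1.6% for planned elective, repeat caesarean birth"), p2 = 0.036, two-sided alpha 0.05, power 80%, difference d = 0.02.

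- At 1:1, n per group = [1.960·√(2·0.026·0.974) + 0.842·√(0.016·0.984 + 0.036·0.964)]² / 0.02², which rounds up to 993. The continuity correction, n/4·[1 + √(1 + 4/(n·d))]², gives 1091 per group, or 2182 in total. The article states 2180.
- At an ERC to VBAC ratio of 6.5:3.5, the same corrected method gives 1490 in the ERC group. The total is 1490 × (1 + 3.5/6.5) = 2292.3, and 2292.3 / 0.99 = 2315.5, so 2316. The article states 2314.

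Both figures reproduce to within two women. They use only the composite rates, so correcting the item changes neither.

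**2. The sign of the criterion.** Input from Primary Study Endpoints: base deficit (BD) < -8. Identity, from standard terminology and not stated in the article: BD = -BE, where BE is base excess. Hence BD < -8 is equivalent to BE > +8.

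| BE | BD | Meets BD < -8 (as written) | Meets BE < -8 (consistent sign) |
|---|---|---|---|
| -16 | +16 | no | yes |
| -12 | +12 | no | yes |
| -9 | +9 | no | yes |
| -8 | +8 | no | no |
| 0 | 0 | no | no |
| +9 | -9 | yes | no |

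Every infant with a positive base deficit fails the written test. The only row that passes is the alkalotic one.

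**3. Who is misclassified in the composite.** Any one item suffices, so an infant with BD above 8 is still an event if cord pH is below 7.18 or another item is met (for example a low five-minute Apgar score, seizures or a long intensive-care stay). The infants lost are those with BD above 8, pH of 7.18 or above, and no other item. The infants wrongly gained are those with BE above +8 and no other item.

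**4. Scale.** The planned overall rate is 0.65 × 1.6% + 0.35 × 3.6% = 2.30%. With 2314 × 0.99 = 2291 women followed, that is 0.023 × 2291 = 52.7 expected events. One misclassified infant is therefore 1 / 52.7, about 1.9%, of the planned event count. How many there would be cannot be derived, because the article gives no distribution of cord-gas values.

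**The case against.** The strongest defence is that the intent is obvious. A clinician who sees the item beside a low pH limit will probably take the minus sign as marking a deficit and apply the intended meaning. The study forms are not shown, and they may already fix the convention. This lowers the chance that the rule is ever applied literally. It does not remove the error: the text states a rule whose term and sign conflict, and nothing else in the article corrects it. Nor is this a detail that an article leaves to the full protocol, since the definition is given and is wrong as given.

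Three stronger readings are tempting, and the article does not support them:

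- A reader might infer that the primary endpoint misses every acidotic infant. It does not; the separate pH item and the other components still capture many of them.
- A reader might size the damage by assuming that 1% to 5% of infants exceed the intended limit, which is 23 to 115 of 2291, or about 44% to 218% of 52.7 events. That proportion is a bare assumption and ignores overlap with the other items. Its upper end exceeds the whole planned composite.
- A reader might infer a bias between groups through centres with different reporting conventions. The article does not say that centres differ in this, or that centre mix differs between the preference groups. In the randomised part, allocation is stratified by centre (Trial Entry). In the preference study, where women choose their group, such a bias is possible; centre is not among the baseline characteristics named in Analysis and Reporting of Results. It remains a risk, not a demonstrated bias.

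**Conclusion.** Wrong as written. Read literally, this component of the primary endpoint selects base excess above +8 and captures no infant with metabolic acidosis. The conclusion rests on the standard relation between base deficit and base excess, and on the adjacent pH item as evidence of intent. The fault may lie in the sign or in the term; the article does not show which.

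The effect is confined to infants who would qualify, or be wrongly counted, through this item alone. Its size in events is unknown. With about 53 events planned, even a few such infants would be noticeable.

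**What to change.** Reconcile the term and the sign with the cited source definitions and with the neonatal form, and state the unit. The most likely wording is base excess < -8 mmol/L (equivalently base deficit > 8 mmol/L), to be confirmed against those sources. The numerical limit itself is not questioned here.

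Have the form record whether each value is a base excess or a base deficit, and derive the component centrally by one rule before outcomes are classified.

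The cost is one corrected line in the endpoint definition and one field on the form. The sample size does not change.

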### Secondary Study Endpoints

1. Serious adverse outcome for the woman is defined as one or more of the following: maternal death; uterine rupture (defined as a clinically significant rupture involving the full thickness of the uterine wall and requiring surgical repair); haemorrhage (blood loss of greater than 1500 mL and/or requiring blood transfusion); hysterectomy for any complications resulting from birth; vulvar or perineal haematoma requiring evacuation; deep vein thrombosis or thrombophlebitis requiring anticoagulant therapy; pulmonary embolus requiring anticoagulant therapy; pneumonia due to infection, aspiration or other causes; adult respiratory distress syndrome; wound infection (requiring prolongation of hospital stay or readmission) or wound dehiscence; damage to the bladder, ureter or bowel requiring repair, or cervical laceration extending to the lower uterine segment, or abnormal extension of the uterine incision; occurrence of a fistula involving the genital tract; bowel obstruction or paralytic ileus; pulmonary oedema; stroke (defined as acute neurological deficit >24 hours); cardiac arrest; respiratory arrest; any other serious maternal complication related to birth (as judged by the adverse events committee, while remaining blinded to group allocation and mode of birth).

Definitions of serious maternal outcomes are based on those considered as important outcome measures of maternal morbidity from The Term Breech Trial [62] and from the ASSHP consensus statement [63].

### Sample Size

The incidence of serious adverse infant outcome is the primary endpoint of the study. The true risk of serious adverse infant outcome is estimated as 1.6% for planned elective, repeat caesarean birth [62]. It is proposed that sufficient women are recruited to provide reliable evidence about the effects of a policy of planned VBAC compared with a policy of planned elective, repeat caesarean on serious adverse infant outcomes. The sample size will detect a change in risk from 1.6% to 3.6% as suggested by the systematic reviews [31]. If the ratio of ERC to VBAC is 1:1 a study of 2180 women would have an 80% power of detecting a statistically significant difference at an alpha level of 0.05 (two tailed). Our pilot study has suggested a ratio of 5.5:4.5. Allowing for an ERC to VBAC ratio of 6.5:3.5 and a small loss to follow up (1%) the sample size required will be 2314 women.

The expected rate of serious maternal complications for planned elective repeat caesarean section is likely to be higher than the 3.9% found in the planned caesarean section arm of the Term Breech Trial [62]. Systematic reviews of the cohort studies of VBAC compared with elective repeat caesarean section provide an estimate of the risks for serious maternal complications of 7.7% [31]. A sample size of 2314 women will have 80% power (2-tailed alpha error of 0.05) of finding the following increases in risk for serious maternal complications: 16% to 20.6%, 12% to 16.1%, 8% to 11.5%, 6% to 9.1% and 4% to 6.7%.

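### The 80% power stated for serious maternal complications does not hold at the 6.5:3.5 split that sets N = 2314; by the plan's own method it is about 75-77%

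*Protocol article*

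**What the plan says.** All the material is in the Sample Size section of the protocol article. For the primary infant outcome (1.6% against 3.6%, two-sided 0.05) it first takes equal groups: "If the ratio of ERC to VBAC is 1:1 a study of 2180 women would have an 80% power". It reports the pilot split, "Our pilot study has suggested a ratio of 5.5:4.5", but sizes the study for a more unequal one, 6.5:3.5, together with 1% loss. On that basis "the sample size required will be 2314 women".

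The next paragraph turns to serious maternal complications, the secondary endpoint, and says: "A sample size of 2314 women will have 80% power (2-tailed alpha error of 0.05) of finding the following increases in risk". The pairs, in per cent, are "16% to 20.6%, 12% to 16.1%, 8% to 11.5%, 6% to 9.1% and 4% to 6.7". That sentence names no allocation ratio and no loss to follow-up, and it does not say which group carries the lower rate.

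**The concern.** The total of 2314 exists only because the plan allowed for a 6.5:3.5 split and 1% loss. A reader will carry that split forward to the maternal sentence, since no other is named there. An unequal split costs power at a fixed total, so a list that fits near-equal groups promises too much at 6.5:3.5. At stake is how a null maternal result is read: the stated differences would be taken as excluded with 80% power when the power is a few points lower. The maternal outcome is the subject of the secondary hypotheses, so the claim will be relied on.

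**Working it through.** **Inputs (Sample Size section).** Primary rates 1.6% and 3.6%; two-sided alpha 0.05; 80% power; N = 2180 at 1:1; N = 2314 at 6.5:3.5 with 1% loss; five maternal pairs; pilot ratio 5.5:4.5. Assumption: the lower maternal rate belongs to ERC, because the paragraph opens with the ERC rate. The reverse is also shown.

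**Step 1: identify the method from the primary figures.** Let k = n2/n1, d = |p1 - p2|, and p̄ the allocation-weighted mean rate. The pooled formula is

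n1 = [1.96·√((1 + 1/k)·p̄(1 - p̄)) + 0.8416·√(p1(1 - p1) + p2(1 - p2)/k)]² / d²

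and the continuity-corrected size is

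n1' = (n1/4)·[1 + √(1 + 2(k + 1)/(k·n1·d))]².

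- 1:1: p̄ = 0.026; (0.4411 + 0.1890)²/0.0004 = 992.6 per group, total 1985. Corrected: 1090.4 per group, total 2180.7. Stated: 2180.
- 6.5:3.5: p̄ = 0.023; (0.4966 + 0.2383)²/0.0004 = 1350.4 in ERC, total 2077.5, or 2099 after dividing by 0.99. Corrected: 1489.8 in ERC, total 2292.1; 2292.1/0.99 = 2315. Stated: 2314.

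The corrected formula reproduces both stated totals to within about one woman. The uncorrected one does not.

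**Step 2: apply the same method to the maternal pairs.** Power = Φ{[d - ½(1/n1 + 1/n2) - 1.96·se0]/se1}, with se0 the pooled and se1 the unpooled standard error.

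Example, 8% against 11.5%, N = 2314:
- 1:1: (0.03414 - 1.96 × 0.01233)/0.01231 = 0.809, power 79.1%.
- 6.5:3.5 (about 1504 and 810): (0.03405 - 1.96 × 0.01261)/0.01321 = 0.706, power 76.0%.

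Higher rate (%) detectable with 80% power, N = 2314, corrected:

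| Lower rate | Listed | 1:1 | 5.5:4.5 | 6.5:3.5 |
|---|---|---|---|---|
| 16 | 20.6 | 20.59 | 20.60 | 20.79 |
| 12 | 16.1 | 16.13 | 16.15 | 16.32 |
| 8 | 11.5 | 11.54 | 11.55 | 11.69 |
| 6 | 9.1 | 9.17 | 9.17 | 9.30 |
| 4 | 6.7 | 6.71 | 6.71 | 6.81 |

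The 1:1 and 5.5:4.5 columns both agree with the list, apart from 9.17 shown as 9.1 (and, at 5.5:4.5, values on a rounding edge). No entry in the 6.5:3.5 column agrees, rounded or truncated.

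Power (%) for the listed pairs at 6.5:3.5, N = 2314:

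| Pair | Corrected | Uncorrected pooled | Corrected, lower risk in VBAC |
|---|---|---|---|
| 16 to 20.6 | 76.8 | 78.5 | 75.7 |
| 12 to 16.1 | 76.1 | 78.0 | 74.6 |
| 8 to 11.5 | 76.0 | 78.2 | 74.0 |
| 6 to 9.1 | 75.4 | 77.9 | 73.0 |
| 4 to 6.7 | 77.1 | 79.9 | 74.3 |

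**Step 3: effect of the 1% loss.** On 2291 evaluable women the corrected powers at 6.5:3.5 become 76.4, 75.7, 75.6, 75.0 and 76.7%. The detectable rates become 20.82, 16.34, 11.71, 9.32 and 6.83%, which are unchanged to one decimal.

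**Step 4: size of the gap in women.** At 6.5:3.5, 80% power for the listed pairs by the corrected formula needs about 2483 (4% to 6.7%) to 2584 (6% to 9.1%) women before loss.

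**The case against.** Three points can be made for the plan.

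First, the pilot ratio is 5.5:4.5, and 6.5:3.5 is a cautious allowance. At 5.5:4.5 and N = 2314 the listed pairs have 78.3-80.0% power corrected and 80.5-82.3% uncorrected, so 80% is about right at the split the pilot suggested. This stands as far as it goes. But the maternal sentence does not say that it uses the pilot ratio, and the paragraph before it fixed N at 6.5:3.5.

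Second, the shortfall depends on the continuity correction. The planned log-binomial analysis carries none, and without it the pooled power at 6.5:3.5 is within about two points of 80%; the 4% to 6.7% pair, at 79.9%, is in effect as stated. This also stands. However, the maternal claim would then rest on a different method from the one that gives 2180 and 2314 in the same section.

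Third, the detectable differences move by only 0.1 to 0.2 percentage points, less than the uncertainty about the baseline rate, which the plan itself spans from 4% to 16%. That limits the importance of the point, though the stated figure is still not the one its own method gives.

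A reader might infer that the authors used exactly 1157 women per group with no loss. The documents do not establish that. At 1:1 the formula gives 9.17 where 9.1 is listed, 5.5:4.5 fits about as well, and 1:1 with 1% loss gives 20.61, 16.16, 11.56, 9.19 and 6.72, which match the list if truncated. Some uncorrected variants at 5.5:4.5 with 1% loss also match all five, for example 20.56, 16.11, 11.51, 9.14 and 6.67 with unpooled variance; these are not the method behind 2180 and 2314.

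**Conclusion.** The point holds in a limited form. Under the method that reproduces the primary sample sizes, the five maternal differences belong to a near-balanced split; whether 1:1 or 5.5:4.5 cannot be determined. At the 6.5:3.5 split that sets N = 2314, with the lower risk in ERC, power falls 3 to 5 points short of the stated 80%. The shortfall is 0 to 2 points without continuity correction, and 4 to 7 points with it if the lower risk is in VBAC.

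It would be wrong to read this as a fault in the primary calculation, which reproduces at 6.5:3.5, or as evidence that the study is too small for its main question. Nor are all five figures materially overstated under every method. This is a misstated figure for a secondary endpoint, with a modest effect on interpretation.

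**What to change.** In the maternal sentence of the Sample Size section, name the allocation ratio, the loss to follow-up, the group assumed to carry the lower rate, and whether a continuity correction is used. Then do one of two things:

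- restate the differences detectable with 80% power at 6.5:3.5 as 16% to 20.8%, 12% to 16.3%, 8% to 11.7%, 6% to 9.3% and 4% to 6.8% (the same to one decimal with or without the 1% loss); or
- keep the listed differences and state power of about 75-77% at 6.5:3.5.

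If the list was meant for the pilot ratio, saying so and adding the power at 6.5:3.5 would also settle it. The cost is one edited sentence. Recruitment, the primary calculation and the analysis stay as they are.

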### Analysis and Reporting of Results

The initial analysis will examine the baseline characteristics of all women in the study, as an indication of comparability of treatment groups. These characteristics will include maternal age, race, height, weight, smoking history, vaginal birth prior to caesarean section, indication for previous caesarean section and treatment preference. Any differences in these prognostic variables that have treatment imbalance of sufficient magnitude will be controlled for in subsequent analyses. Log binominal regression will be used to adjust binary outcomes for confounders and linear regression for normally distributed outcomes. Comparison of outcomes for women and infants will be analysed for the primary and secondary outcomes on an 'intention to treat' basis, according to their planned care at recruitment. The relative risks and 95% confidence intervals will be reported for the major study outcomes, and the number needed to treat to benefit and the number needed to treat to harm will be calculated.
